#### Moving forward

The intervention was developed based on formative qualitative work with African-American breast cancer survivors, followed by a pilot of the guided program that led to further refinements [30, 62].

#### Theoretical framework

The Moving Forward intervention integrates concepts from Social Cognitive Theory (SCT) [63] and the Socio-Ecological Model (SEM) [64, 65] to promote behavior change. SCT suggests that behavior can be explained by the dynamic interaction between behavior, personal factors (e.g., self-efficacy), and the environment (e.g., social support [66–70]. The intervention also incorporates tenets of the socio-ecological model (SEM) [64, 65], a model that goes beyond individual-level variables and emphasizes that support from the larger social context is needed for long-term behavior change [71]. Accordingly, SEM posits that weight status, diet, and physical activity are influenced by individual (e.g., beliefs, taste preferences), interpersonal (e.g., social support, traditions and role expectations), and community factors (e.g., access to resources that support health promotion) [72]. Interventions hoping to promote long-term behavior change must address these three levels of influence [73, 74]. Moving Forward accomplishes this by addressing: (1) Individual factors - acknowledging heavier body image ideals, identifying and addressing personal barriers to behavior change; (2) Interpersonal - the importance of food in the African-American culture and finding ways to integrate this value with healthful eating; providing low-fat versions of culturally traditional “soul food” recipes; acknowledging and addressing family roles and family resistance/support to change; providing information on integrating healthful lifestyle practices for the family; facilitating social support for making changes in diet, physical activity, and weight; understanding the important role of religion and worship in the women’s lives and how it affects their health perspectives and (3) Community - incorporating a sustainable link to a community physical activity resource that can address barriers to regular physical activity (i.e., safety, weather, access); problem solving around cost and availability of healthy food; introducing participants to unfamiliar community resources. Interestingly, a positive sense of community (e.g., social bonds between individuals and between individuals and their community) is associated with self-efficacy for physical activity among African-American women [75].

#### Intervention goals

The overall goal of Moving Forward is to make changes in health behaviors to promote a healthy weight. The weight loss goal is 7 % of baseline body weight (1–2 lbs. per week), consistent with the recommendations of an expert panel at National Institutes of Health [76]. Dietary goals aimed at producing weight loss, decreasing breast cancer recurrence risk, and improving overall health include: (1) a decrease in daily caloric intake (based on weight in pounds X 12 caloriesl/day, with 500–750 cal subtracted to create an energy deficit); (2) a decrease in dietary fat consumption to 20 % of total calories; (3) an increase in fruit and vegetable consumption to 7 daily servings; and (4) an increase in fiber to 25 g per day. For exercise, participants are advised to gradually increase their activity to a minimum of 180 min per week at 55–65 % maximal heart rate.

#### Moving Forward Guided Program Structure (MFG)

The MFG program meets twice a week for 26 weeks (see Table 1 for weekly themes) and is led by a team that includes a community dietitian, a community cancer exercise instructor, and a health psychologist. The program is conducted in city park district facilities, where participants enjoy free memberships, ongoing access to classes and fitness rooms, and the opportunity to maintain contact with program participants once the program concludes. The first meeting each week includes a 60-min class that addresses knowledge (e.g., relationship between obesity and breast cancer; food label reading; portions; available healthy living community resources), attitudes (e.g., pros and cons of weight loss; understanding the roles that food plays in one’s life; the concept of “fail to plan, plan to fail”) and cognitive behavioral strategies including self-monitoring of weight, food and physical activity; realistic goal setting; stimulus control; problem solving; mindfulness; cognitive restructuring and relapse prevention. These classes are led by a dietitian, a psychologist and a certified cancer exercise trainer. Table 1 provides a list of weekly curriculum topics. Pilot data showed that many women entered the program with low levels of knowledge about healthy eating and exercise. Thus, the first weeks are devoted to teaching core concepts (e.g., concept of calories in/out, food label reading, measuring heart rate), while later weeks are focused on cognitive-behavioral aspects of weight loss such as stimulus control, habit and mindfulness. Class activities include weighing in weekly; completing a food and activity self-monitoring record; increasing awareness of portions by weighing and measuring foods according to one’s typical portions and then according to recommended portions; creating stimulus control plans for home, car and work; identifying barriers to healthy eating and/or exercise and problem solving within small groups; going on a field trip to a local grocery store to practice reading food labels; creating an eating-out management plan; and identifying high-risk situations and brainstorming ways to manage them. The first weekly meeting also includes a support “icebreaker” (share the funniest moment of your breast cancer journey; what has been the most frustrating; etc.) and a 60-min exercise class taught by a certified cancer exercise trainer.

**Table 1 Tab1:** Moving forward weight loss program weekly topics

Week 1	Introduction to program
Week 2	Self-monitoring and goal setting
Week 3	Using self-monitoring tools to make better choices
Week 4	Energy requirements
Week 5	Reading food labels and monitoring heart rate
Week 6	Measuring portions
Week 7	Breakfast and water – 2 key tools to losing weight
Week 8	Healthy grocery shopping
Week 9	Meal planning
Week 10	Holiday eating (scheduled according to when holiday falls)
Week 11	Stimulus control
Week 12	Mindful eating
Week 13	Eating away from home – restaurant and party strategies
Week 14	Program review – where were you, where are you now?
Week 15	Building movement into your daily life
Week 16	Barriers to healthy eating and exercise
Week 17	Problem solving
Week 18	The power of habit
Week 19	Strategies to increase fruits and vegetables
Week 20	Where you were, where you are and where you plan to go
Week 21	Relapse preventioin I – what is a lapse vs relapse
Week 22	Relapse prevention II – identifying high risk situations
Week 23	Relapse prevention III – maintaining a physically active lifestyle
Week 24	Relapse prevention IV – motivation to maintain changes
Week 25	Transitioning from Moving Forward to being on your own
Week 26	Graduation

The second weekly meeting is a 60-min exercise class taught by a cancer exercise trainer. The exercise classes incorporate a variety of activities, including traditional aerobics, line dancing, African dance, salsa, yoga, Pilates, and strength and flexibility training. Class time is also spent learning to use the park district fitness facility equipment to ensure that women feel comfortable and competent on the equipment, thus promoting enhanced self-efficacy and mastery of new skills. Many participants enter the program at very low levels of fitness; therefore, physical activity levels are increased gradually with special attention to concerns such as lymphedema and balance. Increased physical activity outside of class is encouraged by suggesting enrollment in additional local exercise classes, providing safe outdoor walking routes, and alerting women to activity resources online and on FitTV.

Participants often need further support and reinforcement of lifestyle changes outside of class, as well as timely information related to healthy eating and exercise resources. To provide this efficiently and effectively, MFG uses text messaging, a strategy successfully used in previous weight loss interventions with low income African-American women [77, 78]. A custom software application, mytapp, allows the psychologist and trainers to schedule two text messages each week to be sent to participants. Messages are less than 200 characters in length and are written to be brief, clear and motivational. The intent is to reinforce concepts covered in class while also supporting self-efficacy, social support and perceived access. For example, during the week that the intervention covers portions, participants receive a text that reads, “Are you using your measuring cups and spoons?” In the week that we cover mindfulness, the message states, “Breathe, Breathe deeply. You CAN savor each bite.” At the end of the six-month program, MFG participants receive six monthly newsletters to review and support concepts related to integrating and maintaining healthy lifestyle habits. They also receive supportive weekly text messages until the final data collection.

#### Moving Forward Self-Guided Program (SG)

Participants randomized to the SG receive a program binder that is divided into 26 sections, with each section addressing the topics listed in Table 1. Within each section is a brief guide to the topic and accompanying worksheets, handouts or activities to complete. Administrative study staff (not intervention staff) meet briefly (approximately 15 min) with the SG participants once individually to give them their binder and to provide an orientation to its layout and contents. Staff follows up with a monthly check-in phone call. At the end of the six months, SG participants also receive the monthly newsletters for six months until the final follow-up data collection.

### Randomization

Approximately one week before the intervention begins at each site, women who completed the baseline visit are randomized in a single block. The allocation assignments for each site are generated using a SAS program written by the data analyst, who has no contact with participants.

A few participants may be unable to complete the baseline visit before the main randomization round. In these cases, the data analyst prepares sealed, numbered envelopes containing the next allocation assignments for the site. As each woman completes her baseline visit, she is assigned the next envelope in the series.

### Statistical analyses

#### Power computations

Calculations were conducted for hierarchical longitudinal designs with differential attrition rates using software provided by Roy et al. [79] Results showed that an initial sample of 240 participants is sufficient to detect an effect size of 0.4, assuming attrition of about 10 % at each time point with power of 0.8 for a two -tailed test. Power will increase with the inter-correlation of observations over time, which we estimated conservatively at 0.4. The addition of covariates to the model will also increase power.

#### Data analysis

For a two-group randomized trial with repeated measures the mixed (multilevel) model is the preferred mode of data analysis [80]. With only two time points, the analysis reduces to a test of the difference between treatment groups in gains or losses in the outcome variable between baseline and 6-month follow up. The model easily generalizes to three time points (including the 12-month visit), in which case time can be indexed in simple linear fashion or represented either in quadratic form or via indicator variables for the first and second follow up measures. In that case, the analysis focuses on between group differences in outcome trajectories over time.

Our hypothesis is that subjects in the MFG condition will experience greater rates of weight loss, improved diet and physical activity patterns and other positive outcomes than subjects in the SG group. A major advantage of casting data analysis in the framework of the generalized linear (regression) model is that it easily accommodates covariates. One important covariate is time since diagnosis, which will be included in all analyses. A potentially important aspect of our modeling will be the investigation of dose–response effects. We will have data on frequency and pattern of attendance for each subject, which will allow us to model outcomes as a function of intensity of treatment.

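### The plan tests raw gains without adjusting for the baseline outcome; at its own correlation of 0.4, baseline adjustment would cut the variance by 30 % at no cost

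*Protocol article*

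**What the plan says.** The Data analysis section of the protocol article chooses a mixed model. For the two-visit comparison, baseline to 6 months, it states that "the analysis reduces to a test of the difference between treatment groups in gains or losses in the outcome variable". When the 12-month visit is added, time may enter linearly, as a quadratic or as visit indicators, and the arms are compared on their trajectories. Time since diagnosis is the one covariate fixed for all analyses. The baseline value of the outcome is not named as a covariate, and no common baseline mean is imposed on the arms.

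The Power computations section says that "an initial sample of 240 participants is sufficient to detect an effect size of 0.4". The power behind this claim is put at 0.80, two-sided, and the calculation allows for a loss of roughly one woman in ten by each visit. On the correlation it says: "Power will increase with the inter-correlation of observations over time, which we estimated conservatively at 0.4". Covariates are expected to raise the power further. The section does not give the alpha, the allocation ratio, the SD that scales the 0.4, or the contrast that was powered.

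**The concern.** A gain score subtracts a woman's whole baseline value. When visits correlate at 0.4, only 0.4 of her baseline deviation carries over to follow-up, so the subtraction adds more noise than it removes. Below a correlation of 0.5 a gain is less precise than ignoring baseline altogether. Baseline adjustment removes only the predictable part; at any correlation below 1 it has a smaller large-sample variance than the gain.

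The plan therefore pairs a planning correlation of 0.4 with the analysis that uses it worst. What is at stake is precision, not bias: under randomisation, both analyses estimate the same arm difference. Outcomes with moderate visit-to-visit correlation would get wider intervals than the data allow, and it is unclear which test the stated 0.80 describes.

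**Working it through.** **Inputs from the Power computations section.** 240 women, effect size 0.4, correlation r = 0.4, about 10 % attrition at each time point, power 0.80, two-tailed.

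**Assumptions.** Alpha 0.05; 1:1 allocation; attrition compounding, so that 240 × 0.9 = 216 women (108 per arm) remain at 6 months and 216 × 0.9 = 194.4 (97.2 per arm) at 12 months; equal SD and equal correlation across visits.

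**The plan's own figure.** A plain two-sample comparison with 0.4 in SDs of the tested variable and 97.2 per arm has power 0.796 (normal) or 0.792 (noncentral t). Equivalently, 99 per arm are needed, and 198 / 0.81 ≈ 245, within 3 % of 240. The 0.80 thus reproduces, but by a calculation that does not use the correlation.

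**Variance per woman, in single-visit SD².**
- Gain: 2(1 − r) = 2 × 0.6 = 1.20
- Follow-up only: 1.00
- Baseline-adjusted: 1 − r² = 1 − 0.16 = 0.84
- Adjusted to gain: (1 − r²) / [2(1 − r)] = (1 + r)/2 = 0.70. Since 1/0.70 = 1.43, the gain test needs about 43 % more women for the same precision.

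**Power if 0.4 is in single-visit SDs.** The standardised effect is 0.4/√variance: 0.365 for the gain, 0.400 for follow-up only, 0.436 adjusted. Noncentral t on women with the visit:

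| Visit | Gain | Follow-up only | Baseline-adjusted |
|---|---|---|---|
| 6 months (216) | 0.762 | 0.833 | 0.891 |
| 12 months (194.4) | 0.717 | 0.792 | 0.857 |

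The gain test needs about 237 analysed women for 0.80. With 216 it reaches 0.80 at r of about 0.45.

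**Mixed model on all available data** (10 %, 9 % and 81 % of women with one, two and three visits; normal approximation):

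| Contrast | Baseline mean free in each arm | Common baseline mean |
|---|---|---|
| 6 months | 0.778 | 0.894 |
| 12 months | 0.748 | 0.863 |

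With free baseline means and an effect of 0.4 at both follow-ups, the joint two-degree-of-freedom test has noncentrality 9.77 and power 0.806. The average of the two follow-ups has 0.878.

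**Power if 0.4 is in SDs of the change score.** The gain test has 0.833 at 6 months and 0.792 at 12. The adjusted effect is 0.4/√0.70 = 0.478, giving 0.938 and 0.912.

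**Higher correlations (single-visit scale, normal approximation).** At r = 0.7 the 6-month power is 0.967 for the gain and 0.984 adjusted. At r = 0.9 the variance ratio is (1 + 0.9)/2 = 0.95 and both powers are about 1.0.

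**The case against.** A reader might infer that the trial misses its stated 0.80 power. The documents do not support that, for three reasons.

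- The scale of the 0.4 is undefined. In change-score SDs the gain test has 0.83 at 6 months and 0.79 at 12, so the stated figure is roughly met. The remark that power rises with the correlation suggests single-visit SDs, since it would not apply to a two-visit gain test already scaled on the change SD. It does not say so.
- The powered contrast is undefined. The calculation was for a hierarchical longitudinal design, and the joint two-visit test with a sustained effect gives 0.81 without any baseline adjustment. That effect pattern is an assumption too, but so is every other choice of contrast.
- The gain-test sentence covers two time points only. The 12-month figure of 0.72 belongs to a complete-case gain test that the plan does not describe. For that visit the relevant figures are those of the mixed model, 0.75 against 0.86.

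Three further points are fair. The 0.4 is called conservative, and the benefit shrinks as the correlation rises. BMI, a leading outcome, may track closely; the article gives no outcome-specific correlations. The covariate named is not said to be the only one, and an unshown analysis plan may list more.

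These points remove the claim of a power failure and limit the size of the gain. They do not remove the efficiency point. The article states the test of gains outright, and adjustment improves on it under either scale of the effect size.

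**Conclusion.** The concern holds as one of precision. At the plan's own correlation the gain test is the least precise of the three standard analyses, and adjusting for the baseline outcome reduces the variance by 30 %.

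In power terms the size is conditional. With 0.4 in single-visit SDs, 6-month power rises from about 0.76 (0.78 in the mixed model) to 0.89, and the 12-month mixed-model contrast from about 0.75 to 0.86. With 0.4 in change-score SDs, it rises from about 0.83 to 0.94 at 6 months and from 0.79 to 0.91 at 12. All figures rest on two-sided 0.05, 1:1 allocation and r = 0.4; the mixed-model figures also need the correlation to be equal between all visits. For outcomes with r near 0.9 the variance saving is only about 5 %. A shortfall against the stated 0.80 is possible but not shown.

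**What to change.** Analyse every outcome with baseline adjustment, in one of two forms:

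- a mixed model with one baseline mean shared by both arms and arm-by-visit terms at 6 and 12 months; or
- ANCOVA with the baseline value of the outcome as a covariate, alongside time since diagnosis.

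In the power section, state which SD scales the 0.4, the alpha, the allocation ratio and the contrast that is powered. Then restate the power for the adjusted analysis at about 216 women at 6 months and 194 at 12 months.

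The cost is revised analysis wording and a restated power paragraph. The baseline assessment already precedes randomisation, so no new data or participants are needed.

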**Fig. 2 Fig2:**
[figure not shown]
Study Conceptual Framework. The independent variable is group assignment. It is expected that outcome results will be mediated by self efficacy at the individual level, social support at the interpersonal level and perceived access to healthy eating and exercise resources at the community level

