### Intervention

Participants are randomized to either the Moving Forward Guided program (MFG) or the Moving Forward Self-Guided program (SG) for six months. MFG includes in-person classes and text messaging, while the SG includes a curriculum manual with handouts related to the intervention topics, but no classes or text messaging.

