## Discussion

This novel study examines the efficacy of a community-based weight loss program for African-American breast cancer survivors. Few behavioral interventions have targeted this high-risk population. Observational data highlight unhealthy eating and sedentary physical activity patterns among African-American breast cancer survivors, while qualitative data document their interest in making lifestyle changes to lose weight [62, 81]. Unfortunately, many survivors (regardless of race) are confused by the various dietary and physical activity recommendations, struggle with effective weight loss strategies, and relate a need for more structured programming [62]. Urban African-American women face further barriers in their quest to practice healthy lifestyles. Many African-Americans in the general population live in economically stressed neighborhoods where access to fresh fruits and vegetables may be limited or cost prohibitive, but cheaper high-fat foods are easily accessible [82, 83]. In addition, opportunities for physical activity in disadvantaged communities are often limited by a lack of safe open spaces, sidewalks in disrepair, gang violence, poor lighting, and insufficient police [84]. Focus groups with African-American breast cancer survivors highlight other important barriers, as well as facilitators. Barriers include pain, family commitments and lack of social support; facilitators include faith and spirituality, family and friend support, and desire to reduce overall health risks and risk of recurrence [62, 81]. If lifestyle change interventions are to be successful, barriers and facilitators must be addressed.

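### The planned attendance dose–response analysis rests on a self-selected, post-randomisation exposure that varies only in the guided arm, so it can show a dose effect when classes have none

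*Protocol article*

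**What the plan says.** The Data analysis section makes the comparison by randomised group the main analysis: with three time points, "the analysis focuses on between group differences in outcome trajectories over time". It then adds a second line of work: "A potentially important aspect of our modeling will be the investigation of" dose–response effects. The reason given is the availability of "data on frequency and pattern of attendance for each subject, which will allow us to model outcomes as a function of intensity of treatment".

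The Intervention section describes SG as a curriculum manual with handouts, "but no classes or text messaging". The section on the self-guided program adds one orientation meeting of about 15 minutes and a monthly check-in call. Sessions exist only in the other arm: "The MFG program meets twice a week for 26 weeks".

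One covariate is named for every model: "One important covariate is time since diagnosis, which will be included in all analyses". The article does not say whether the attendance model is confined to MFG, how SG enters it, or whether its result is to be read as an association or as an effect.

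**The concern.** The article fixes three things: the exposure (attendance), the direction of the model (outcome on attendance) and the reading (dose–response, intensity of treatment). Following them leads to two difficulties.

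First, attendance data for every woman carry no information on dose in SG, where the value is zero for all. All variation in attendance beyond the arm contrast lies within MFG, so a gradient estimated there is not protected by randomisation.

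Second, women decide how often to come. The article itself names plausible common causes of attendance and outcome. On lifestyle change, the Discussion says: "Barriers include pain, family commitments and lack of social support". The Fig. 2 legend says: "It is expected that outcome results will be mediated by self efficacy at the individual level", and adds social support and perceived access. Time since diagnosis is not a measure of any of these. Classes also include a weekly weigh-in, so early weight loss could itself encourage further attendance.

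At stake is the interpretation. An attendance gradient described as a dose–response effect could be taken as evidence that the classes work, even beside a small or null randomised difference.

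**Working it through.** **Sample size for the check.** The plan gives no figure for the attendance analysis, so its overall sample size is reproduced first. Inputs from Power computations: effect size 0.4, power 0.8, two-tailed, about 10% attrition at each time point, N = 240. Assumed because not stated: alpha 0.05 and 1:1 allocation.

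- n per arm = 2(1.960 + 0.842)² / 0.4² = 98.1, or 99 with the t correction (198 in total).
- Two successive 10% losses leave 0.81: 99 / 0.81 = 122.2, so 123 per arm, 246 in total. This is close to 240.
- With 120 × 0.81 = 97.2 per arm, power is 0.796 against the stated 0.80.

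The sample size is not in dispute. At 6 months it leaves 120 × 0.9 = 108 MFG women.

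**False gradient with no class effect.** Let a factor U (motivation, or freedom from barriers) correlate a with attendance and b with weight loss, with no effect of classes. The attendance–outcome correlation is then a × b. By Fisher's z, the chance of p < 0.05 is about Φ(atanh(ab)·√(n − 3) − 1.96), plus a negligible opposite tail.

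- a = b = 0.3, n = 108: ab = 0.09; 0.0902 × 10.247 = 0.925; chance 15%.
- a = b = 0.4: ab = 0.16; 0.1614 × 10.247 = 1.654; chance 38%.
- a = b = 0.5: ab = 0.25; 0.2554 × 10.247 = 2.617; chance 74%.
- a = 0.5, b = 0.4, n = 120: ab = 0.20; 0.2027 × 10.817 = 2.193; chance 59%.

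**Simulation.** 1,500 trials per scenario, 108 women per arm, true class effect zero, attendance with assumed mean 60% and SD 25 points, truncated to 0–100%, and no covariates. Entries are the share of trials with p < 0.05.

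| r (= a = b) | MFG only | Both arms, SG = 0, arm term | Both arms, SG = 0, no arm term | Randomised comparison | Mean false slope in MFG, 0% to 100% attendance |
|---|---|---|---|---|---|
| 0 | 0.05 | 0.05 | 0.04 | 0.05 | 0 SD |
| 0.3 | 0.16 | 0.16 | 0.09 | 0.05 | 0.40 SD |
| 0.4 | 0.38 | 0.37 | 0.13 | 0.05 | 0.68 SD |
| 0.5 | 0.74 | 0.73 | 0.24 | 0.06 | 1.04 SD |
| 0.6 | 0.97 | 0.97 | 0.43 | 0.06 | 1.51 SD |

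Adding SG at zero with an arm term changes nothing, because SG supplies no variation in attendance. Omitting the arm term mixes the randomised contrast with the self-selected gradient, which dilutes the bias but does not remove it. At r = 0.3 the mean false slope already equals the effect size of 0.4 on which the trial is powered, though it is expressed over the whole attendance range.

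**What an instrument would give.** With arm as the only instrument and SG at zero, the estimate is the randomised difference divided by mean sessions in MFG, out of a maximum of 2 × 26 = 52. It is one number and holds no information on shape. On the assumed attendance figures, the pooled dose has variance (0.60/2)² + 0.25²/2 = 0.121, so SD 0.348. The correlation of arm with dose is 0.30/0.348 = 0.86. The interval is then about 1/0.86 = 1.16 times as wide as that of a pooled regression on attendance without an arm term.

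**The case against.** The article gives the attendance analysis two sentences. It states no model form, population or full covariate set, and an article may leave these to a fuller plan. A reader might infer that an unadjusted regression is fixed, but the text does not say so. It names time since diagnosis as one important covariate, not the only one, and says the model accommodates others. Several plausible confounders are measured at baseline: comorbidity, social support, self-efficacy, perceived access, fatigue and symptoms. Eligibility also requires physician approval and the ability to attend twice weekly, which narrows health-driven non-attendance. The simulation adjusts for none of this, so its rates are for the unadjusted case. Zero is also a legitimate dose for SG, so the reference to every subject is loose wording rather than a fatal contradiction.

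These points limit the size of the problem and stand. They do not remove it. Exposure, direction and dose–response reading are stated, with nothing to mark the result as non-causal. Measured covariates can reduce self-selection but cannot be assumed to eliminate it.

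An instrument has limits too. Text messages and free park membership with access to fitness rooms also differ by arm, so the instrumented effect cannot be credited to sessions alone.

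**Conclusion.** The point holds in a limited form. As described, the attendance analysis can show a dose–response without any class effect, and under moderate confounding it often would. Without adjustment, about 15% to 75% of trials would show a false gradient within MFG for assumed correlations of 0.3 to 0.5, against 5% with no common cause. The correlations, and the attendance mean and SD in the simulation, are assumptions with no source in the documents.

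Two stronger readings are not supported. One is that the analysis is bound to report a dose effect: at correlations of 0.3, about 85% of trials would not. The other is that the trial's efficacy result is compromised, or that dissemination will turn on attendance. The main comparison is by randomised group and keeps its error rate (5% to 6% throughout). The article ties dissemination to the success of the intervention and does not mention attendance there. The change is worth making because a non-randomised association is at present described as a dose–response effect.

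**What to change.** In the Data analysis section:

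1. State that attendance is zero by design in SG and that the attendance gradient is estimated within MFG.
2. Label that gradient exploratory and non-causal, and keep it out of the efficacy conclusion.
3. Adjust it for baseline factors already collected: baseline outcome, self-efficacy, social support, comorbidity, fatigue and symptoms. Say that residual self-selection remains possible.
4. If a causal estimate of receiving the programme is wanted, use randomised arm as the instrument for sessions attended. Report it as an effect of the guided package, because text messages and free park access also differ by arm.

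The cost is some wording and a little programming; no new data are needed. The instrumented interval is wider than that of a pooled regression on attendance (about 1.16 times on the assumed figures). The estimate only rescales the randomised difference and says nothing about the shape of a dose–response.
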